**Methods/Design:**

Following quasi-experimental design, the intervention is conducted in two secondary schools located in the district of Hulu Langat, Selangor, Malaysia. Adolescents aged 13–14 years will be included in the study. A peer-education strategy is adopted to convey knowledge and teach skills relevant to achieving a healthy lifestyle. The intervention mainly promoted: healthy eating, positive body image and active lifestyle. The following parameters will be assessed: body weight, disordered eating status, stages of change (for healthy diet, breakfast, food portion size, screen viewing and physical activity), body image, health-related quality of life, self-esteem, eating and physical activity behaviours; and knowledge, attitude and practice towards a healthy lifestyle. Assessment will be conducted at three time points: baseline, post-intervention and 3-month follow-up.

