## Methods/Design

### Study design

EPaL is a school-based intervention programme targeting adolescents in the early years of secondary school. The present study adopted a quasi-experimental design, in which adolescents from one school were included in the intervention group, while those from another school served as the comparison group and were not subjected to the intervention until the end of the period of experimentation. Adolescents in the comparison group attended a standard physical and health education class at least once a week. As the study was concluded, they were allowed to receive EPaL modules and educational materials. A flowchart of the intervention is shown in Fig. 1.

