### Measurements

All participants in both the intervention and the comparison schools will be assessed prior to the beginning of the programme (baseline assessment), after the final session of the intervention (post-intervention assessment) and 3 months afterwards (follow-up assessment).

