### Data analysis

Data will be analysed by using version 21 of the IBM SPSS Statistical software (IBM SPSS Statistics, Inc., Chicago, IL, USA). Depending on the distribution of the variable of interest, descriptive statistics of continuous data will be presented by using the mean and standard deviation, and the median and the inter-quartile range. Categorical data will be presented as frequencies and percentages. *T*-test will be used to detect differences between groups for continuous variables, while chi-square will be used to investigate possible correlations between categorical variables. The repeated measures analysis of variance (ANOVA) will be used to detect significant differences within the groups. The evaluation of the intervention will be based on an intention-to-treat analysis. Differences with *p*-values < 0.05 were considered significant.

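### No stated analysis compares change between the two schools: the between-group t-test ignores baseline and is tied to no visit, and repeated-measures ANOVA is confined to within-group differences

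*Protocol article*

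**What the plan says.** Under Study design, "adolescents from one school were included in the intervention group, while those from another school served as the comparison group". The Discussion lists as a limitation that randomisation reached only the schools, not the pupils. The abstract states that "Assessment will be conducted at three time points: baseline, post-intervention and 3-month follow-up", and Measurements applies this to both arms: "All participants in both the intervention and the comparison schools will be assessed prior to the beginning of the programme", with the two later assessments following.

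The Data analysis section gives each test a role:

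- **t-test:** it "will be used to detect differences between groups for continuous variables". No visit is named, nor whether levels or changes are compared, and no baseline adjustment is mentioned.
- **Chi-square:** "chi-square will be used to investigate possible correlations between categorical variables". Neither group nor time appears in this sentence.
- **Repeated-measures ANOVA:** "The repeated measures analysis of variance (ANOVA) will be used to detect significant differences within the groups".

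Two general statements follow. One fixes the analysis set: "The evaluation of the intervention will be based on an intention-to-treat analysis". The other sets the threshold: differences with p-"values < 0.05 were considered significant". Neither says which contrast decides whether EPaL worked.

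**The concern.** The trial exists to learn whether pupils offered EPaL change more than pupils who have their usual health education class. Both schools are measured three times, so the data can answer that. The analyses as described divide the question in two. One test compares the schools without using time or baseline, and the other uses time without comparing the schools. Neither estimates the difference in change.

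This matters more here than in a trial that randomises individuals. Two whole schools can differ at baseline in weight, eating attitudes or quality of life, and chance balance between pupils cannot be relied on. A comparison of levels after the programme carries such a difference straight into the result. The Background also places these pupils at the age of puberty and rising body fat, so some change in both schools is likely without EPaL. A significant within-school change is therefore not evidence of an effect in itself.

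**Working it through.** **Inputs from the article.** 234 pupils per group, 5% significance, 80% power, and proportions of 40.3% and 27.9% (Sample size calculation); three assessments (Measurements); one school per arm (Study design).

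**Assumed inputs.** Size of the baseline gap between schools, size of a common time trend, and within-pupil correlation. The article gives none of these.

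**Step 1: the plan's own figure.** The arcsine effect size is h = 2·asin(√0.403) − 2·asin(√0.279) = 0.263. Then n = 2·((1.96 + 0.842)/0.263)² ≈ 228 per group, against 234 stated, which is within 3%. (The article's own effect size, 0.254, would give 244; this has no bearing here.) I use 234 below.

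**Step 2: unadjusted t-test of levels, no EPaL effect, stable gap between schools.** The standard error of a difference in means, in SD units, is √(2/234) = 0.0925. For a gap d, the chance of p < 0.05 two-sided is approximately Φ(d/SE − 1.96) + Φ(−d/SE − 1.96).

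| Assumed gap d (SD) | d/SE | Chance of a significant difference |
|---|---|---|
| 0 | 0 | 5% |
| 0.1 | 1.08 | 19% |
| 0.2 | 2.16 | 58% |

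Half an SD is not needed: a gap of a fifth of an SD is enough to make a false finding more likely than not. A contrast of change from baseline has expectation d − d = 0, so it removes a stable gap.

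**Step 3: setting the two within-group results against each other.** Suppose both schools change equally, and let p be the chance that either one's change is significant. The schools are independent, so the chance that the intervention school alone is significant is p(1 − p).

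| p | p(1 − p) |
|---|---|
| 0.05 (no drift) | 4.75% |
| 0.20 or 0.80 | 16% |
| 0.30 or 0.70 | 21% |
| 0.50 | 25% (maximum) |

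Counting discordance in either direction doubles these figures, but half of those cases have only the comparison school significant, and nobody would read that as success for EPaL.

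**Step 4: simulation.** Settings: 234 per school, three visits, within-pupil correlation 0.6, the same shift after baseline in both schools, no baseline gap, no school-level clustering, 3,000 replicates. The share of replicates with only the intervention school significant was:

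| Common shift (SD) | Intervention school only |
|---|---|
| 0 | 5% |
| 0.05 | 11% |
| 0.10 | 23% |
| 0.13 | 24% |
| 0.15 | 19% |
| 0.20 | 5% |

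The rate falls again at larger shifts because both schools then become significant. Across all settings, including a 0.30 SD shift, the group-by-time test rejected in 4.2% to 5.7% of replicates and the post-intervention t-test in 4.4% to 5.5%. The t-test result depends on the schools starting equal, which this design does not ensure; Step 2 shows what happens when they do not.

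**The case against.** The strongest reply is that a between-group test is planned. The t-test sentence comes before the ANOVA sentence, and categorical variables are given to chi-square, so ANOVA is not being forced onto binary or ordinal outcomes. That is correct. A reader might infer from the ANOVA sentence that EPaL will be declared effective if its school's change is significant and the other school's is not. The article does not say so. The hypothesis in the Discussion, worded as improvement after the programme, leaves that reading open but does not adopt it. The rates in Steps 3 and 4 therefore hold only under a rule that is not in the plan. They also require the common change to run in a direction that would be called favourable, and they approach 25% only over a middle range of drift.

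It can also be said that a journal article condenses, and that the visit for the t-test, the use of change scores or the exact model may stand in a fuller plan. That is fair as to detail, and I make no point of the choice between one longitudinal model and another. What stands is that the article states a role for its one longitudinal method, and that role is within-group. The comparison of change is not merely left unspecified: the method that could supply it is assigned to another question. For disordered eating, the outcome on which the sample size rests, the chi-square sentence names no group contrast, and a chi-square at one visit would again compare levels.

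**Conclusion.** The concern holds in this form: as written, no stated analysis tests whether pupils in the EPaL school change more than pupils in the comparison school. The main exposure is the unadjusted comparison of levels, with about 19% false positives at an assumed stable gap of 0.1 SD and about 58% at 0.2 SD. These figures use a normal approximation with 234 per group and assume the t-test is applied to post-intervention or follow-up levels. If it were applied to change scores, this exposure would disappear, but the article does not say that.

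The second exposure, reading the within-group results against each other, is conditional on a rule that the plan leaves open. Its rate in EPaL's favour is about 5% without drift and at most 25%; that ceiling does not depend on the assumed correlation or trend. The documents do not support the stronger claims that no between-group test is planned, or that effectiveness will be judged from paired within-group p-values.

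**What to change.** In the Data analysis section, name the between-group difference in change from baseline as the test of EPaL. Either of two forms would do:

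- a group-by-time term over the three visits, reported as contrasts at post-intervention and at 3 months; or
- a baseline-adjusted between-group contrast at each of those two visits.

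Give confidence intervals. Use a logistic equivalent for disordered eating and other binary outcomes. Report within-group changes as description only.

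Choose one form in advance, because in non-randomised schools the two can differ. If a stable gap d persists and the within-pupil correlation is r, baseline adjustment leaves d(1 − r). With d = 0.2 SD and r = 0.6 (both assumed) that is 0.08 SD, whereas the change contrast leaves none.

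The cost is analysis wording and syntax, with no new data. The change does not separate the effect of the school from that of the intervention: with one school per arm, a school-specific trend would still look like an EPaL effect, and the report should say so.

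### Intention-to-treat is promised, but the within-group repeated-measures ANOVA (as usually run) and the per-visit between-group tests use different subsets, and none uses all data from every enrolled student

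*Protocol article*

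**What the plan says.** The Data analysis section of the protocol article sets out both the principle and the tests.

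- Principle: "The evaluation of the intervention will be based on an intention-to-treat analysis".
- Change over time: "The repeated measures analysis of variance (ANOVA) will be used to detect significant differences within the groups".
- Between groups, continuous outcomes: the t-test "will be used to detect differences between groups for continuous variables".
- Categorical outcomes: "chi-square will be used to investigate possible correlations between categorical variables".
- Software: SPSS version 21. The procedure for the repeated-measures analysis is not named.

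The abstract fixes the schedule: "Assessment will be conducted at three time points: baseline, post-intervention and 3-month follow-up". The Measurements section applies it to all participants in both schools. The Sample size calculation section asks for 234 students per group and states no allowance for loss. The article does not define the intention-to-treat set, and it mentions neither imputation nor deletion of incomplete cases.

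**The concern.** A conventional repeated-measures ANOVA over three occasions needs a value at each occasion. Unless missing values are filled in first, a student with one gap is removed from it altogether. A t-test or chi-square test at a given visit needs only that visit. The same outcome would therefore be reported on one set of students for change over time and on other sets for the group comparisons, all described as intention-to-treat.

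Two things are at stake.

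1. **Selection.** One school attends eight club sessions over 16 weeks, while the other continues with its standard class. Missed assessments could plausibly differ between the schools and be related to engagement, weight or eating attitudes. This is a reasoned risk; the article gives no evidence on it either way.
2. **Information.** The ANOVA is the only named method that takes the three occasions together, and it is the one that discards partial records.

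**Working it through.** **Inputs.** From the Sample size calculation section: proportions 40.3 % and 27.9 %, power 80 %, significance level 5 % (two-sided assumed), 234 per group, effect size by arcsine transformation. From the abstract: three assessments, of which two come after baseline. The loss rate is not given, so 5, 10, 15 and 20 % are assumed below.

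**Step 1: reproduce the plan's figure.**

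h = 2·arcsin√0.403 − 2·arcsin√0.279 = 1.3756 − 1.1130 = 0.2626

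n = 2(1.960 + 0.842)² / h² = 227.7, so 228 per group. The pooled two-proportion formula gives 229.

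Both are within 3 % of 234, so the stated size is reproduced closely enough to serve as the base. Power at 234 is Φ(0.2626·√(234/2) − 1.96) = Φ(0.880) = 0.81.

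**Step 2: students kept by each method.** Let m be the share missing each follow-up visit, independently, with baseline complete.

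- ANOVA, all three visits needed: 234·(1 − m)²
- t-test or chi-square at one follow-up visit: 234·(1 − m)

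| m | ANOVA keeps | One-visit test keeps | Difference per group |
|---|---|---|---|
| 5 % | 211 | 222 | 11 |
| 10 % | 190 | 211 | 21 |
| 15 % | 169 | 199 | 30 |
| 20 % | 150 | 187 | 37 |

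If instead every loss is a permanent drop-out before the first follow-up, the same students are missing at both visits. Both methods then keep 222, 211, 199 or 187 per group, and the gap between them closes.

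**Step 3: power for the between-group contrast.** The 40.3 % versus 27.9 % contrast is a comparison of two proportions, which the plan assigns to chi-square, so the one-visit numbers apply. Power = Φ(0.2626·√(n/2) − 1.96), ignoring clustering by school:

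| m | n per group | Power |
|---|---|---|
| 0 | 234 | 81 % |
| 5 % | 222 | 79 % |
| 10 % | 211 | 77 % |
| 15 % | 199 | 74 % |
| 20 % | 187 | 72 % |

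The pooled formula agrees to within 0.2 percentage points in each row. No power figure is given for the within-group ANOVA, because the article states no effect size or correlation for it.

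**Step 4: compare the sets.** Intention-to-treat in full means every enrolled student, analysed in the group of the school. The ANOVA uses students with all three visits. The post-intervention tests use students seen then, and the follow-up tests use students seen three months later. With any loss at all, none of these is the enrolled set.

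**The case against.** The strongest reply is that the text contains no outright contradiction. Listwise deletion is what a conventional repeated-measures ANOVA does by default; the article does not state it as a rule. Imputing first would fit every word of the section. How missing assessments are handled is also something a journal article commonly leaves to the full protocol or analysis plan. This stands: silence on imputation alone would not be a finding. What remains is that the section does fix its methods, and those methods as usually run do not deliver the principle stated beside them.

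A reader might go further and infer that the whole evaluation is in fact complete-case. The article does not support that. It gives the ANOVA only the task of finding differences within the groups, and the between-group tests do not need all three visits.

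A reader might also put the three-visit numbers (211, 190, 169, 150) into the power formula and report 77, 72, 68 and 62 %. That applies the ANOVA's deletion to a contrast that chi-square would test at a single visit, and at 20 % loss it roughly doubles the fall in power (81 to 62 % instead of 81 to 72 %).

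Nor do the named tests conflict with the other half of intention-to-treat, which is analysing students by school whatever their session attendance. The Measurements section plans to assess all participants in both schools, so leaving the club is not the same as missing an assessment.

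**Conclusion.** The point holds in a limited form. An intention-to-treat evaluation is promised, but the ANOVA named for within-group change, run conventionally, drops students with any missing assessment, and the between-group tests use whoever is present at each visit. The analyses rest on different subsets, and none uses all data from every enrolled student.

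Under independent losses of 5 to 20 % per follow-up visit, the ANOVA would use 11 to 37 fewer students per group than a one-visit test. Power on the sample-size contrast would fall from 81 % to between 79 and 72 %. These figures rest on assumed loss rates, independent misses, complete baseline data, a two-sided 5 % test and no clustering. With permanent drop-out the difference between methods shrinks or disappears, although the loss from the enrolled set remains. The direction and size of any bias cannot be judged from the article.

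**What to change.** Define the intention-to-treat set as all enrolled students, analysed by the school they enrolled in whatever their session attendance. Replace the repeated-measures ANOVA with:

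- a linear mixed model for continuous outcomes;
- a logistic mixed model or GEE for binary outcomes such as disordered eating.

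Use all available assessments, with group, time, group-by-time and baseline terms, and base the evaluation on the between-group contrast at each follow-up. State whether baseline is one of the repeated occasions or a covariate. If it is a covariate, students with neither follow-up contribute nothing unless their values are imputed.

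If the ANOVA is to stay, either impute before running it and say how, or label it complete-case.

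**Cost.** No new data are needed, only changed wording and somewhat more analysis work. The mixed model relies on data being missing at random. GEE needs a stricter condition unless it is weighted or combined with imputation. Neither approach recovers all the information in an unobserved follow-up value, so the power lost to missed visits would be regained only in part.

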### Sample size calculation

The sample size calculation was based on the differences between groups (overweight and obese; and non-overweight and non-obese) in the proportion of having disordered eating. The value was taken from the outcome of needs assessment study, which was conducted involving 9677 adolescents aged 12–19 years throughout Malaysia. Based on the study, the proportion of overweight and obese adolescents who were having disordered eating was 40.3 %, whereas the proportion of non-overweight and non-obese adolescents who were having disordered eating was 27.9 %. Assuming a power of 80 % and a level of significance of 5 %, we needed 234 participants for each intervention and comparison groups, respectively. The effect size for proportions was estimated by the differences in the arcsine transformations of the respective proportions. The medium effect size of 25.4 % was obtained.

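### No primary outcome or primary visit is named among about 15 unranked outcomes, each open to a claim at p < 0.05, so the chance of at least one false positive is far above 5%

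*Protocol article*

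**What the plan says.** The abstract (Methods/Design) states: "The following parameters will be assessed: body weight, disordered eating status", then "stages of change (for healthy diet, breakfast, food portion size, screen viewing and physical activity", then body image, health-related quality of life, self-esteem, eating and physical activity behaviours, and knowledge, attitude and practice. None is ranked above another. On timing it says: "Assessment will be conducted at three time points: baseline, post-intervention and 3-month follow-up". The Measurements section repeats this schedule for both schools.

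In Data analysis, the t-test "will be used to detect differences between groups for continuous variables", chi-square serves categorical variables, and repeated measures ANOVA "will be used to detect significant differences within the groups". One threshold covers them all: p "values < 0.05 were considered significant".

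The article gives several indications of what success would be, and they differ:
- Sample size calculation uses the difference "in the proportion of having disordered eating", comparing overweight or obese adolescents with the rest. It does not call this outcome primary.
- The abstract's Background and the Background section aim at preventing both overweight and disordered eating.
- The abstract's Discussion expects effects on body weight status, lifestyle behaviour and quality of life.
- The opening hypothesis of the main Discussion names body weight status, healthy lifestyle and quality of life. It leaves out disordered eating, the one outcome used for sizing.

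**The concern.** A reader cannot tell from the article which result would count as EPaL having failed. With many outcomes, two later visits, one unadjusted threshold and no deciding outcome, the conclusion could rest on whichever comparison turns out favourable. A positive headline would then carry much less evidence than its p-value suggests. A body-weight result, a knowledge score and one stage-of-change item would all have the same formal standing.

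**Working it through.** **The plan's own figure.** The only outcome-specific calculation is 234 per group for 40.3% versus 27.9%, 80% power and 5% significance (taken as two-sided). The arcsine effect size is h = 2·asin(√0.403) − 2·asin(√0.279) = 0.2626, so n = 2(1.960 + 0.842)²/0.2626² ≈ 228. A normal-approximation formula gives 229. Both are within 3% of 234, so the figure is reproduced. (The article's stated effect size of 0.254 would need 244, which does not affect this point.) The calculation therefore fits a single test at 0.05 on disordered eating, but the rest of the plan does not single out that test.

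**Counting outcomes** (abstract): body weight 1, disordered eating 1, stages of change 5, body image, quality of life, self-esteem, eating behaviour and physical activity behaviour 5, knowledge, attitude and practice 3. Total 15. Two visits after baseline give 15 × 2 = 30 between-group tests. Grouping the list into 8 domains gives 16 tests. The measurement sections contain further scores and subscales; an illustrative 39 gives 78 tests.

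**If tests were independent and EPaL had no effect:**
- Any p < 0.05, 15 tests: 1 − 0.95^15 = 54%. For 30 tests: 1 − 0.95^30 = 78.5%.
- Favouring EPaL only (2.5% per test), 15 tests: 1 − 0.975^15 = 32%. For 30 tests: 1 − 0.975^30 = 53.2%.

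**With correlation.** The document gives no correlations, so these are assumptions: 0.2-0.7 between outcomes and 0.5-0.7 between the two visits. Multivariate-normal simulation, 200,000 draws, two-sided threshold 1.96. Each cell shows any significant result / results favouring EPaL.

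| Tests | Independent | Correlation 0.2-0.5 | Correlation 0.7 |
|---|---|---|---|
| 16 (8 domains) | 56.0% / 33.3% | 38-51% / 19-28% | 30-32% / 15-16% |
| 30 (15 outcomes) | 78.5% / 53.2% | 53-72% / 27-41% | 39-42% / 20-21% |
| 78 (39 scores) | 98.2% / 86.1% | 76-95% / 40-66% | 54-58% / 27-30% |

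The expected number of false positives does not depend on correlation. For 30 tests it is 30 × 0.05 = 1.5 in either direction, or 30 × 0.025 = 0.75 in EPaL's favour.

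The within-group ANOVA tests are not counted here.

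**The case against.** A reader might infer that a false claim of effectiveness is more likely than not. The documents do not support that, for four reasons.
- The 54% and 79% count significant results in either direction. A false claim that EPaL works needs a result in its favour.
- In that direction, 30 tests pass 50% only under independence. Independence is implausible: the same adolescents are measured repeatedly, the five stages of change are related, and knowledge, attitude and practice come from one questionnaire. With the correlations assumed above, the figure is about 20-41%.
- Nowhere does the article say that one significant result would mean success. It says only which differences are called significant, and its hypotheses name several effects together.
- The count of 30 is inferred from the schedule. Data analysis does not tie the t-test or chi-square to each later visit.

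It is also fair to say that a condensed article may leave the multiplicity method and testing order to a fuller document. That stands for the adjustment method. It does not cover the deciding outcome, which is core protocol content and belongs in the sample size, measurement and analysis sections that the article does contain. The article also reports that registration was retrospective, so prospective registration cannot be assumed to have fixed a primary outcome.

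Finally, one could treat disordered eating as the implied primary because it drives the sample size. That reading is weakened by the main Discussion's hypothesis, which omits it. In addition, the two rates come from a survey comparison of weight-status groups and are not an expected difference between intervention and comparison schools.

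**Conclusion.** The point holds in this form: no primary outcome or time point is designated, one unadjusted threshold covers every difference, and the article's own indications of success disagree. Over the 30 inferred tests, the chance of at least one false positive is roughly 40-80%, or about 20-53% in EPaL's favour, against nominal rates of 5% and 2.5%. Even the lowest of these is several times nominal.

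The figures assume no effect on any outcome, two-sided testing, each outcome tested at both later visits, and correlations that the document does not give. They also assume that each test is valid at its own level. With one school per arm and individual-level tests, that need not be so, and these figures do not include that problem.

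**What to change.** Before analysis, amend the protocol wording as follows.

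1. Name one primary outcome at one named visit, tested at 0.05. EAT-26 disordered-eating status is the natural candidate, because it is the only outcome in the sample size calculation. The sponsor should confirm this choice, given that the rates used there are not an intervention effect.
2. Because preventing overweight is a joint aim, either test BMI-for-age z-score next in a fixed sequence, only if the primary is significant, or make the two co-primary with alpha split between them (for example 0.025 each).
3. Report all other outcomes with confidence intervals as supportive, with no effectiveness claim from their p-values.

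Bonferroni over all 30 tests is the alternative, at 0.05/30 = 0.00167 per test, which is far more demanding.

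The cost is wording, plus fewer outcomes that can be called significant. An equal alpha split also costs power. On the plan's own rates with 234 per group, h·√(234/2) = 0.2626 × 10.82 = 2.84. Power is then Φ(2.84 − 1.96) = 81% at 0.05 and Φ(2.84 − 2.24) = 73% at 0.025, ignoring any school effect. The fixed sequence avoids that loss for the first outcome.

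This change settles outcome selection and multiplicity only. A single primary tested at 0.05 does not guarantee a 5% error rate while school and intervention are confounded, with one school in each arm.
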